### 2.1 Study registration

This study will be registered in the Clinicaltrials.gov (a registry listed in the WHO International Clinical Trials Registry Platform (ICTRP)).

In addition, registration French will be entered in the Swiss National Clinical trial Portal (SNCTP via BASEC).

### 2.2 Categorisation of study

#### Oclin category A

- The interventions assessed are the PCR on saliva and the RDT on nasopharyngeal swab against the reference test, which is the PCR on nasopharyngeal swab. RDTs are CE approved.

#### Oclin category C

- The intervention assessed is the RDT on saliva against the reference test, which is the PCR on nasopharyngeal swab. RDT are CE approved.

### 2.3 Competent Ethics Committee (CEC) and Competent Authorities (CA)

**Protocol approval.** The principal investigator ensures that approval from an appropriately constituted Competent Ethics Committee (CEC), and Swissmedic is sought for the clinical study OclinC.

**Protocol changes.** No changes are made to the protocol without prior approval from the Sponsor and CEC, except where necessary to eliminate apparent immediate hazards to study participants. Such urgent changes to the protocol due to immediate hazards must be reported to the Sponsor within 48h. According to Oclin art. 37 safety and protection measures which must be taken immediately will be notified to CER-VD.

**Unanticipated risks/benefits.** This is an observational prospective trial that features very little additional risk to the patient. The collection of saliva swabs is innocuous. The standard procedure for nasopharyngeal swab can be accompanied (very rarely) by lesion of the nasal mucosa. It definitely leads to some discomfort, or even pain, for the patient.

Should this study show a case detection rate for SARS-CoV-2 using RDT on saliva of at least 70% of that using the standard method (nasopharyngeal PCR), this new method could be proposed as standard diagnostic testing procedure for testing of ambulatory COVID-19 suspected cases to the cantonal and national health authorities, as well as to the national COVID-19 task force. It should ease the work of the testing teams and lead to less

discomfort for patients, and hence probably higher rate of testing readiness from symptomatic patients. The overall testing expenses per person will also be considerably reduced.

The threshold of 70% has been chosen to take into account that RDT on saliva or PCR on saliva are expected to have an overall detection rate lower than that of naso-pharyngeal PCR, but possibly much higher if patients with very low viral loads (e.g. 1000 copies/ml) are excluded from the analysis (Jacot et al, in press). The detection of the virus in the latter patients is indeed fluctuating strongly from one sample or one moment to another. Moreover, they probably contribute much less to transmission than patients with higher viral loads.

A particular effort will be made to expedite reporting and wide communication, given the global urgency of the COVID-19 testing situation.

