In addition, Rapid Diagnostic Tests for the detection of SARS-CoV-2 antigens have been developed using nasopharyngeal swabs and have shown very high sensitivity against PCR, ranging from 93% to 98% when based on laboratory validation. [see summary table from [name] (unpublished) in Appendice 2 and Kruger et al <https://www.medrxiv.org/content/10.1101/2020.10.01.20203836v1>]. This method offers the considerable advantage to inform the patient of the test result on site, and allow the provision of appropriate recommendations on the spot of testing. The studies performed so far have been conducted using nasopharyngeal samples only. There are no data with saliva yet. It is expected that the RDT would also work on the saliva. Even if slightly less sensitive due to the fact that it detects antigens and not multiplied RNA as PCR does, RDT on saliva could better serve the public health goal to test widely and quickly and have ultimately more COVID cases detected and isolated, and hence reduced transmission.

To investigate the case detection rates of both PCR on saliva and nasopharynx and RDT on nasopharynx and saliva, we intend to take four samples, two swabs on saliva, one for RDT and one for PCR, and two swabs on nasopharynx, one for RDT and one for PCR. Patients who have at least one of the common symptoms and who consent to such a procedure will be recruited to compare the four results. Our primary objective is to compare the case detection rates for SARS-CoV-2 of the four testing methods (two sampling types and two test types). Since we may not have RDT and Swissmedic approval at the very start of the trial, we may introduce the different new tests step by step.

To be precise, we write 'saliva sample', but precisely we mean gingivo-buccal swab sample, and this thereafter in the document.

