| 
Procedures:
 | 
Patients fulfilling inclusion and exclusion criteria will be recruited consecutively from the two testing sites of Unisanté (Bugnon 44 et Flon) and two testing site in town (Centre medical de la Source and Vidy-Med). After confirmation of inclusion and exclusion criteria (except for anticoagulation that will be asked later), patients will be asked whether they would be willing to provide two saliva samples and one nasopharyngeal swab in addition to that provided for routine testing. After written informed consent, patients will be asked to perform swabbing of the gingiva-buccal fold two times under professional supervision, once for sending to the laboratory to perform PCR, and once for performing the RDT onsite according to the below procedure. They will be taken two nasopharyngeal swabs, one for RDT and one for PCR.
 
The RDTs will be performed and results read according to the manufacturer information (see below).
 
The saliva and nasopharyngeal samples will be handled according to the procedures usually used for nasopharyngeal swabs. Samples will be forwarded to the Institute of Microbiology where they will be analysed by PCR according to the standard procedure (Corman et al 2020, Greub et al 2016, Pillonel 2020).
 
The patient will be considered as positive for SARS-CoV-2 if any of the PCR results or the RDT result on nasopharynx is positive. Indeed, the specificity of these three tests have been shown to be close to 100%. Moreover, in the presence of a suboptimal standard test (PCR on nasopharyngeal swab), it is possible to have higher or differential detection rate with the new tests. The result of the RDT on nasopharynx will be given on the spot because this test has now been validated in a clinical trial (https://www.medrxiv.org/content/10.1101/2020.10.01.20203836v1). The provision of an immediate response may decrease the refusal rate. Since the RDTs are less sensitive than PCR, we will inform patients who receive a negative RDT result that they have to wait for confirmation by PCR analysis before lifting isolation measures. PCR results will be forwarded to the patients using routine channels, the final result being negative if the two PCR and the RDT on nasopharynx are negative, or positive if any of these three tests are positive.
 
Because of problems in RDT availability and need for Swissmedic approval for the Oclin C component, we may start step by step:
 
 
1) PCR on saliva and nasopharyngeal swab
 
2) When RDT are available: PCR on saliva and nasopharyngeal swab + RDT on nasopharyngeal swab.
 
3) When RDT available and Swissmedic approval granted, all four components, namely PCR on saliva and nasopharyngeal swabs, RDT on saliva and nasopharyngeal swab.
 
 |

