### 3.3 Statistical Analyses

#### 3.3.1 Primary analysis

##### Primary outcome:

- Proportion of SARS-CoV-2 positive patients by testing method (RDT vs PCR) and sampling type (saliva vs nasopharyngeal).

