##### Study analysis population

All patients recruited will form the study analysis population. All samples will be analysed, except if a patient withdraws his consent after collection and before analysis of his/her sample. If the microbiological test has already been done, we will keep the result in the overall analysis and the patient will still be informed of his/her result due to the fact that it is the public health benefit that prevails over that of the individual.

The proportion of SARS-CoV-2 positive patients (detection rate) and 95% confidence intervals by any method will be presented. Then the detection rate of each method will be compared to that of all other three methods combined (best possible detection rate, true positives).

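### The stated basis for proposing saliva RDT as a standard test has no false-positive condition, and as detection rate is defined, false positives can help it pass

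*Protocol*

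**What the plan says.** Section 2.3, under the paragraph on risks and benefits, gives one condition: "a case detection rate for SARS-CoV-2 using RDT on saliva of at least 70% of that using the standard method (nasopharyngeal PCR"). If it is met, "this new method could be proposed as standard diagnostic testing procedure for testing of ambulatory COVID-19 suspected cases". The reason given for the figure concerns missed cases only: "The threshold of 70% has been chosen to take into account that RDT on saliva or PCR on saliva are expected" to find fewer cases than nasopharyngeal PCR, mainly at low viral load. False positives are not mentioned.

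The primary outcome in section 3.3.1 is "Proportion of SARS-CoV-2 positive patients by testing method (RDT vs PCR) and sampling type (saliva vs nasopharyngeal"). The same section equates this proportion with the detection rate: "The proportion of SARS-CoV-2 positive patients (detection rate) and 95% confidence intervals by any method will be presented". It then says that "the detection rate of each method will be compared to that of all other three methods combined (best possible detection rate, true positives").

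On specificity, the synopsis (Procedures) names the two PCRs and the nasopharyngeal RDT and says: "Indeed, the specificity of these three tests have been shown to be close to 100" per cent. Saliva RDT is not among the three, and it is also absent from the list in section 2.6 of tests whose positive result is taken as true. On RDT with saliva, the synopsis (Background and Rationale) says: "There are no data with saliva yet". The synopsis also classes this use as outside the manufacturer's instructions.

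The interim rule in section 3.3.2 (200 patients, about 40 positive) stops saliva RDT, or replaces the RDT type, if it detects under 50% of the patients found by the two PCRs combined, or over 20% of them. The rule for nasopharyngeal RDT has only the 50% limb.

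**The concern.** A criterion based on detection alone cannot distinguish a test that finds cases from one that often reads positive. Here it is applied to the one test that the protocol does not itself trust to call a patient positive. A saliva RDT with many false positives could meet the stated condition for being proposed to the cantonal and national authorities. If detection rate means the proportion positive, a test of poor sensitivity could also meet it, because its false positives would make up the shortfall.

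The results needed to see this are collected (section 5.1.1 records all four results for each patient), but the condition in section 2.3 does not use them.

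**Working it through.** **Inputs from the protocol.** 1250 patients, of whom 250 positive, hence 1000 not (section 3.2). Interim at 200 patients with about 40 positive, hence 160 not (section 3.3.2). Threshold 0.70 (section 2.3).

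**Assumptions.** The protocol gives neither sensitivity (Se) nor specificity (Sp) for saliva RDT, so both are varied. Nasopharyngeal PCR is taken to find all 250 cases with no false positives.

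**The plan's own figure.** 1.96 × √(0.20 × 0.80 / 1250) = 2.2 points, which agrees with the stated ±2% after rounding. It describes the proportion positive and says nothing about specificity.

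**Reading A: detection rate as the proportion positive.** Ratio = [Se × 250 + (1 − Sp) × 1000] / 250. A pass needs 0.70 × 250 = 175 positives.

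| Assumed Se | Assumed Sp | True positives | False positives | Total | Ratio |
|---|---|---|---|---|---|
| 50% | 100% | 125 | 0 | 125 | 0.50 (fail) |
| 60% | 97.5% | 150 | 25 | 175 | 0.70 (pass) |
| 50% | 95% | 125 | 50 | 175 | 0.70 (pass) |
| 40% | 92.5% | 100 | 75 | 175 | 0.70 (pass) |
| 30% | 90% | 75 | 100 | 175 | 0.70 (pass) |

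At Se 50%, lowering Sp from 100% to 95% turns a fail into a pass.

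**Reading B: detection counted among cases only.** The ratio equals Se, so Se 70% (175 true positives) passes whatever Sp is. Positive predictive value (PPV) = 175 / (175 + false positives).

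| Assumed Sp | False positives | PPV |
|---|---|---|
| 99.5% | 5 | 97% |
| 98% | 20 | 90% |
| 95% | 50 | 78% |
| 90% | 100 | 64% |

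**The interim clause.**
- Literally: any percentage is either below 50 or above 20, so one limb or the other always triggers.
- If the upper limb means more than 20% above PCR: it acts above 1.2 × 40 = 48 positives. Se 70% with Sp 90% gives 28 + 16 = 44, and the test continues. At Se 70% the limb acts only if false positives exceed 48 − 28 = 20 of 160, that is, Sp below 87.5%.
- The lower limb, if counted among PCR-positive patients, would on expected counts catch Se 40% (16 of 40) and Se 30% (12 of 40). It would not catch Se 50% (20 of 40) or Se 60% (24 of 40).

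**Precision available for specificity.** 1.96 × √(Sp × (1 − Sp) / 1000) = 0.44, 0.87, 1.35 and 1.86 points at Sp 99.5, 98, 95 and 90%. This assumes about 1000 uninfected patients with all four results, which matches the aim in section 3.2 of 250 positives with all four sample types.

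**The case against.** Several points on the other side have force.

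- **The sentence in section 2.3 is permissive.** It says that the method could be proposed, in a paragraph on risks and benefits and outside the statistical section. A reader might infer a binding adoption rule, or a proposal to use saliva RDT entirely on its own. The text states neither. It is, however, the only basis stated for the proposal, and its threshold is argued for.
- **There is an interim clause.** A reader might infer that nothing in the plan looks at over-calling. The upper limb in section 3.3.2 applies to saliva RDT only and may have been meant for that. It is garbled, applies at one interim look, and on its most charitable reading misses specificities near 90%.
- **Antigen specificity is discussed.** Section 2.6 calls it excellent, and Appendice 2 lists 99.40% and 99.68% for two of the three brands in use. At those values Reading B gives 6 and 3.2 false positives and PPVs of 175/181 = 97% and 175/178.2 = 98%. A reader might infer from the lower rows that saliva RDT is poorly specific. Nothing in the protocol shows that. Equally, the appendix figures are for nasopharyngeal swabs and cannot be carried over to saliva.
- **Prevalence.** The week-35 positivity of 11% to 14% would make the PPVs worse, but it was measured irrespective of symptoms. The protocol expects 20% under its inclusion criteria, and that figure is used here.
- **Participants.** Saliva RDT does not enter the result given to the patient, so its false positives isolate nobody within the trial.
- **The analysis plan may report specificity.** It may, and its absence from the protocol's outcomes is not the fault. Reporting alone would still leave the condition in section 2.3 one-sided.

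**Conclusion.** The point stands in a limited form. The stated basis for proposing saliva RDT has no false-positive condition, and this concerns the one test with no specificity claim and no saliva data. If detection rate is the proportion positive, as section 3.3.1 has it, false positives count towards the 70%: Se 50% with Sp 95%, or Se 60% with Sp 97.5%, just passes. If it is counted among cases, Se 70% passes at any specificity, with PPV between 97% and 64% over the assumed range of 99.5% to 90%. These figures rest on 20% prevalence, an error-free nasopharyngeal PCR, and assumed values for saliva RDT.

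The fault lies in the criterion. The data are collected, and no harm to participants follows. It should be corrected before the results are used to support a proposal.

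**What to change.** 1. In section 2.3, compute the 70% among reference-positive patients only, so that a saliva RDT positive in a reference-negative patient does not count.
2. In section 3.3.1, add saliva RDT specificity with a 95% confidence interval among patients negative on all three other tests, with PPV at the observed prevalence. This reference agrees with the case definition in the synopsis and with the three-method comparator in section 3.3.1. A reference based on the two PCRs alone would conflict with both, because the protocol treats a patient positive on nasopharyngeal RDT as a case.
3. In section 2.3, make the proposal also conditional on the lower 95% limit for specificity exceeding a minimum that the sponsor states, with its reason, before the data are seen.
4. In section 3.3.2, reconcile the upper limb for saliva RDT with its lower limb and say what each percentage is a percentage of.

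The cost is a few sentences, with no new samples, visits or patients. The one downside is that saliva RDT could then fail on false positives.

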## **2.4 Ethical Conduct of the Study**

The study will be carried out in accordance to the protocol and with principles enunciated in the current version of the Declaration of Helsinki, the guidelines of Good Clinical Practice (GCP) issued by ICH, the Swiss Law and Swiss regulatory authority's requirements. The CEC and regulatory authorities will receive the final report and be informed about study stop/end in agreement with local requirements.

## **2.5 Declaration of interest**

The investigators in this trial have no conflict of interest to declare.

## **2.6 Patient Information and Informed Consent**

### **Recruitment**

- Patients meeting inclusion criteria will be informed about the objectives of the study and given an information sheet. They will be asked for their consent to have a gingivo-buccal and a nasopharyngeal swabbing for PCR, a nasopharyngeal swab for RDT and a gingivo-buccal one for RDT (possibly only two or three swabs, depending on RDT availability and Swissmedic approval). They will be informed about the fact that any positive test (be it from nasopharyngeal PCR, saliva PCR, or nasopharyngeal RDT) will be considered as true positive (and not false positive) because of the excellent specificity of the Ag used for RDT and primers for PCR. This is based also on the principle of precaution since there is no risk of isolating a possible negative symptomatic patient, but there is definitely a public health issue to leave a positive subject being in contact with friends and colleagues.
- No financial compensation will be provided for participation.
- The cost of the routine procedure (nasopharyngeal swab) will be supported by the Direction générale de la santé (DGS) as usual.

## **2.7 Participant privacy and confidentiality**

The investigator affirms and upholds the principle of the participant's right to privacy and that they shall comply with applicable privacy laws. Especially, anonymity of the participants shall be guaranteed when presenting the data at scientific meetings or publishing them in scientific journals.

Individual subject medical information obtained as a result of this study is considered confidential and non-anonymised disclosure to third parties is prohibited.

For data verification purposes, authorised representatives of the Principal investigator, a competent authority (e.g. Swissmedic), or an ethics committee may require direct access to parts of the medical records relevant to the study, including participants' medical history.

## 2.8 Early termination of the study

The Principal investigator may terminate the study prematurely according to certain circumstances, for example:

- ethical concerns,
- when the safety of the participants is doubtful or at risk, respectively,
- alterations in accepted clinical practice that make the continuation of a clinical trial unwise.

## 2.9 Protocol amendments

Substantial amendments are only implemented after approval of the CER-VD.

Under emergency circumstances, deviations from the protocol to protect the rights, safety and well-being of human subjects may proceed without prior approval of the sponsor and the CER-VD. Such deviations shall be documented and reported to the sponsor. According to OClin art. 37, safety and protection measures which must be taken immediately will be notified to CER-VD within 7 days.

All non-substantial amendments are communicated to the CER-VD.

An adaptive design may be appropriate in this trial since new tests may become available and also new knowledge accumulates very rapidly and may affect our design or procedures.

## 3. STATISTICAL METHODS

Statistical analysis will be undertaken jointly by the investigators and [name]

### 3.1 Hypothesis

This trial seeks to compare SARS-CoV-2 detection rates by RDT on saliva, RDT on nasopharynx, PCR on saliva and PCR on nasopharynx.

The primary hypothesis is that the proportion of patients detected positive by SARS-CoV-2 RDT is not less than 20% of that of a composite PCR test result (saliva + nasopharynx PCR results combined).

### 3.2 Determination of Sample Size

|                              |                                                                                                                                                                                                                                                                                                                                                             |
|------------------------------|-------------------------------------------------------------------------------------------------------------------------------------------------------------------------------------------------------------------------------------------------------------------------------------------------------------------------------------------------------------|
| Sample size predicted | 
250 SARS-CoV-2 positive patients (from either RDT or PCR on saliva and nasopharynx) corresponding to ~1250 patients enrolled
 
 
- 1250 RDT on saliva samples
 
- 1250 PCR on saliva samples
 
- 1250 RDT on nasopharyngeal samples
 
- 1250 PCR on nasopharyngeal samples
 
 |
|------------------------------|-------------------------------------------------------------------------------------------------------------------------------------------------------------------------------------------------------------------------------------------------------------------------------------------------------------------------------------------------------------|

Currently the number of tests performed daily in the canton de Vaud are >1000 at the different triage sites.

At Unisanté, in week 35, we had 398 tests performed at Bugnon 44 with 55 positive (14%), and 749 performed at the Flon with 80 positives (11%), irrespective of symptoms. At Centre Médical de la Source and Vidy-Med, at least 100 patients are tested every day.

The proposed sample size of 250 positive among 1250 cases tested will allow to have a precision of  $\pm 2\%$  on the detection rate if the latter is 20%, based on a confidence interval of 95%.

Since we may start with only PCR swabs and RDT on nasopharyngeal swab, we may need to slightly increase the sample size to meet our objectives of 250 positives with all four types of samples. A calculation will be performed at the time of interim analysis to potentially adapt the sample size. The protocol will be amended at that time and CER-VD approval sought if there is a modification.

